### Measures

Sociodemographic characteristics, smoking history, smoking cessation treatment history, depression history, and depression treatment history will be assessed using a face-to-face structured interview. In addition, the following instruments will be used (Table 1 lists the measures collected at each time point):Smoking Habit Questionnaire [35], consisting of 56 items designed to gather information both on sociodemographic variables (gender, age, marital status, educational level) and tobacco use (i.e., number of cigarettes smoked per day).Fagerström Test for Cigarette Dependence (FTCD) [36]. It is made up of six items for the assessment of cigarette dependence. Scores ≥6 are considered to be indicative of dependence [37]. Cronbach’s alpha coefficient was.60 in studies conducted in Spain [38].Nicotine Dependence Syndrome Scale (NDSS) [39, 40]. Questionnaire based on multidimensional conceptualization of substance dependence as a syndrome. The reliability of the general factor that evaluates nicotine dependence is good, Cronbach’s alpha was.80.Nicotine Withdrawal Scale Minnesota (MNWS) [41]. This is an 8-item scale measuring nicotine withdrawal symptoms (depression, insomnia, irritability/frustration/anger, anxiety, difficulty concentrating, restlessness, increased appetite/weight gain) and craving (desire or urge to smoke, which is considered independently). It is an instrument with good reliability, with a Cronbach’s alpha was.85.Structured Clinical Interview, according to DSM-5 criteria for assessing tobacco use disorder.Screening Questionnaire Major Depressive Episode (MDE) [42]. This is an instrument to detect past and current major depressive episodes.Beck Depression Inventory II (BDI-II) [43, 44]. This is a 21-item self-report scale measuring current depressive symptoms. The internal consistency obtained in Spanish sample with Cronbach’s alpha was.90.Hamilton Depression Rating Scale (HDRS) [45, 46]. This instrument was designed to quantitatively assess the severity of depressive symptoms and to monitor changes. The internal consistency obtained with a Cronbach’s alpha was.72.The Environmental Reward Observation Scale (EROS) [47, 48]. This is a brief self-report measure designed to obtain efficient, reliable, and valid information on the amount and availability of environmental reward. The Spanish version has a good internal consistency; Cronbach’s alpha was.86.Behavioral Activation for Depression Scale (BADS) [49, 50]. This 25-item questionnaire was designed to measure four basic dimensions of the behavioral activation model: Activation, Avoidance/Rumination, Work/School Impairment, and Social Impairment. The scale shows good internal consistency with Cronbach’s alpha was .90 for the total score, .81 for the Activation subscale, .82 for the Avoidance/Rumination subscale, .76 for the Work/School Impairment subscale, and .88 for the Social Impairment subscale.Ruminative Response Scale (RRS) [51, 52]. The RRS is a 22-item self-report for assessing ruminative coping responses to depressed mood. Treynor and colleagues [53] found that 12 items from the RRS overlapped with depressive symptoms, so that the resulting 10-item version will be used. The RRS Spanish version has been found to show adequate psychometric properties with Cronbach’s alpha scores for brooding and reflection of .73 and .72, respectivelyUCLA Loneliness Scale (Version 3) [54, 55]. This is a highly reliable instrument to measure loneliness, with a Cronbach’s alpha was .94.Carbon monoxide in expired air assessment. We will use the Micro + Smokerlyzer (Bedfont Scientific Ltd., Maidstone, Kent, U.K.) to measure carbon monoxide (CO) in expired air so as to corroborate self-reported abstinence at the end of treatment and at follow-ups, as suggested in previous studies [56].

**Table 1 Tab1:** Timeline for data collection across the trial

Measures	Measurement time-point				
	Baseline	End of treatment	3-month follow-up	6-month follow-up	12-month follow-up
Smoking Habit Questionnaire	X				
TUS, Tobacco DSM-5 criteria	X				
MDE	X				
UCLA	X				
RRS	X				
FTCD	X	X	X	X	X
+NDSS	X	X	X	X	X
MNWS	X	X	X	X	X
BDI-II	X	X	X	X	X
HRDS	X	X	X	X	X
EROS	X	X	X	X	X
BADS	X	X	X	X	X
CO	X	X	X	X	X

*TUS* Tobacco Use Disorder, *MDE* Screening Questionnaire Major Depressive Episode; *UCLA* Loneliness Scale; *RRS* Ruminative Response Scale; *FTCD* Fagerström Test of Cigarette Dependence; *NDSS* Nicotine Dependence Syndrome Scale; *MNWS* Minnesota Nicotine Withdrawal Scale; *BDI-II* Beck Depression Inventory II; *HDRS* Hamilton Depression Rating Scale; *EROS* Environmental Reward Observation Scale; *BADS* Behavioral Activation for Depression Scale; *CO* carbon monoxide in expired air

### Intervention conditions

#### Standard cognitive-behavioral smoking cessation treatment

The standard cognitive-behavioral smoking cessation treatment is a manualized treatment for tobacco dependence, called “Smoking Cessation Program” [57]. The treatment components are: treatment contract, self-report and graphic representation of cigarette consumption, information about tobacco, nicotine fading [change of cigarette brands each week, progressively decreasing the intake of nicotine and tar), stimulus control, activities to prevent withdrawal syndrome, physiological feedback (CO in expired air) on cigarette consumption, and relapse-prevention strategies (assertion training, problem-solving training, changing tobacco-related misconceptions, management of anxiety and anger, exercise, weight control, and self-reinforcing). Treatment will be delivered in eight 60-min sessions over 8 consecutive weeks.

#### Standard cognitive-behavioral smoking cessation treatment and behavioral activation

Behavioral Activation will be applied along with the previously described standard cognitive-behavioral smoking cessation treatment. The treatment elements are the above-mentioned ones plus the following: analysis of the relationship between behavior and mood, identification of situations and behaviors that decrease mood, identifying avoidance behaviors, and identifying rumination and worry, self-report of pleasant daily activities, pleasant activity scheduling to increase engagement in rewarding activities and to reduce patterns of behavioral avoidance. Treatment will be delivered in eight 60-min sessions over 8 consecutive weeks.

#### Treatment delayed control group

It will be a delayed-treatment control group for a period of 3 months. After the 3-month period, another assessment will be carried out, and then participants will be offered to participate in a smoking cessation treatment (Table 2).

**Table 2 Tab2:** Summary of session-by-session outline of intervention procedures

Ss	Cognitive-behavioral Smoking Cessation Treatment (CBSCT)	CBSCT + Behavioral Activation
1	Overview of treatment Smoking cessation treatment rationale Review self-monitoring (tracking cigarettes and smoking antecedents and consequences) Indications about how to graphically represent the No. of cigarettes/day Reasons for smoking and for quitting Discuss smoking history and quit experiences Explain and provide written materials about tobacco, nicotine dependence, smoking health consequences and quit smoking benefits Explain nicotine fading through brand change Physiological feedback (CO) As homework: - Brand change - Communicate to at least one person [family, friend, coworker, etc.) that he/she is trying to quit smoking in the next 30 days - Not smoke more cigarettes than the average of those smoked the previous week - Leave a third of the cigarette without smoking - Refuse cigarette offers	Overview of treatment Smoking cessation treatment rationale Review self-monitoring (tracking cigarettes and smoking antecedents and consequences) Indications about how to graphically represent the No. of cigarettes/day Reasons for smoking and for quitting Discuss smoking history and quit experiences Explain and provide written materials about tobacco, nicotine dependence, smoking health consequences and quit smoking benefits Explain nicotine fading through brand change Physiological feedback (CO) As homework: - Brand change - Communicate to at least one person (family, friend, coworker, etc.) that he/she is trying to quit smoking in the next 30 days - Not smoke more cigarettes than the average of those smoked the previous week - Leave a third of the cigarette without smoking - Refuse cigarette offers
2	Check homework and nicotine fading compliance Continue smoking self-monitoring and analyze smoking behavior during the week Physiological feedback (CO) Discuss brand change difficulties New brand change and reduce No. of cigarettes Review importance of social support Introduce stimulus control technique to remove situations conditioned to smoking Nicotine withdrawal and strategies to avoid it Breathing exercises and relaxation techniques (practice as homework)	Check homework and nicotine fading compliance Continue smoking self-monitoring and analyze smoking behavior during the week Physiological feedback (CO) Discuss brand change difficulties New brand change and reduce No. of cigarettes Review importance of social support Introduce stimulus control technique to remove situations conditioned to smoking Nicotine withdrawal and strategies to avoid it Breathing exercises and relaxation techniques (practice as homework)
3	Check nicotine fading, cigarette reduction and stimulus control compliance Check breathing exercises compliance and strategies to avoid withdrawal symptoms Physiological feedback (CO) Continue cigarette self-monitoring and analyze smoking behavior New brand change and reduce No. of cigarettes Continue stimulus control technique Explain and provide written materials for weight control and exercise Continue with breathing exercises and strategies to avoid withdrawal symptoms	Check nicotine fading, cigarette reduction and stimulus control compliance Check breathing exercises compliance and strategies to avoid withdrawal symptoms Physiological feedback (CO) Continue cigarette self-monitoring and analyze smoking behavior New brand change and reduce No. of cigarettes Continue stimulus control technique Explain and provide written materials for weight control and exercise Continue with breathing exercises compliance and strategies to avoid withdrawal symptoms Rationale of mood influence in smoking cessation [provide written materials) Homework: daily activities self-monitoring
4	Check nicotine fading, cigarette reduction and stimulus control compliance Check breathing exercises compliance and strategies to avoid withdrawal symptoms Physiological feedback (CO) Continue smoking self-monitoring and analyze smoking behavior New brand change and reduction of No. of cigarettes Continue stimulus control technique Stress and anxiety management strategies Problem-solving training	Check nicotine fading, cigarette reduction and stimulus control compliance Check breathing exercises compliance and strategies to avoid withdrawal symptoms Physiological feedback (CO) Continue smoking self-monitoring and analyze smoking behavior New brand change and reduction of No. of cigarettes Continue stimulus control technique Stress and anxiety management strategies Check activity scheduling and encourage recognizing patterns of depressed behavior and the way in which engaging in enjoyable and important activities may impact their overall mood Homework: continue activity scheduling, create a pleasant activities list and choose one to do during the week
5	Check nicotine fading, cigarette reduction, and stimulus control compliance Physiological feedback (CO) Continue smoking self-monitoring and analyze smoking behavior New brand change and reduction of No. of cigarettes Management of anxiety and anger Self-reinforcing Changing tobacco-related misconceptions	Check nicotine fading, cigarette reduction, and stimulus control compliance Check activity scheduling, pleasant activities list elaboration, and pleasant activity compliance Physiological feedback (CO) Continue smoking self-monitoring and analyze smoking behavior New brand change and reduction of No. of cigarettes Management of anxiety and anger Self-reinforcing Changing tobacco-related misconceptions Problem-solving training Recognize avoidance behavior and impact on mood Activity scheduling and engagement in 2 pleasant activities/week
6	Quitting experience and withdrawal symptoms Physiological feedback (CO) Discuss and plan for high-risk lapse and relapse situations Motivating factors for maintaining abstinence Benefits of quitting smoking Common barriers for maintaining abstinence	Quitting experience and withdrawal symptoms Physiological feedback (CO) Discuss and plan for high-risk lapse and relapse situations Motivating factors for maintaining abstinence Benefits of quitting smoking Common barriers for maintaining abstinence Ruminative thoughts, smoking cessation process, and relapse Check activity scheduling and pleasant activity compliance Activity scheduling for the next week and engagement in 2 pleasant activities/week
7	Quitting experience and withdrawal symptoms Physiological feedback (CO) Discuss and plan for high-risk lapse and relapse situations Motivating factors for maintaining abstinence Benefits of quitting smoking Strategies for relapse prevention	Quitting experience and withdrawal symptoms Physiological feedback (CO) Discuss and plan for high-risk lapse and relapse situations Motivating factors for maintaining abstinence Benefits of quitting smoking Review how behavioral activation impacts their overall mood Review avoidance behavior and ruminative thoughts’ significance Strategies for relapse prevention
8	Physiological feedback (CO) Managing the future as ex-smokers Encouragement for abstinence maintenance Support for lapses and relapse Review motivating factors, lifestyle changes, physical and cognitive-behavioral health improvement Treatment conclusion and management of potential obstacles	Physiological feedback (CO) Managing the future as ex-smokers Encouragement for abstinence maintenance Support for lapses and relapse Review motivating factors, lifestyle changes, physical and cognitive-behavioral health improvement Review BA strategies Treatment conclusion and management of potential obstacles

### Therapist

Trained therapists (Master level in clinical or counseling psychology) will conduct the assessment and intervention sessions.

### Treatment manual

Both treatments have been manualized with the aim of training the therapist and improving the intervention implementation. Both of them include a detailed session-by-session protocol and follow-up procedures.

### Intervention fidelity

All sessions will be video-recorded to supervise the therapist and to assess intervention fidelity. Study supervisors will assess fidelity through the random visualization of treatment sessions in both active arms.

### Outcomes

#### Primary outcome measures

Point-prevalence abstinence defined according to Russell Standard (RS) criteria [56]. Participants will be considered abstinent if they report abstinence, not even a puff of a cigarette, for ≥24 h at the end of treatment, and for ≥7 days prior to follow-up day at the 3-month follow-up, and have an expired carbon monoxide reading of ≤10 ppm. At the 6- and 12-month follow-ups, participants will be considered abstinent if they report abstinence, not even a puff of a cigarette, for ≥30 days prior to follow-up day, and have an expired carbon monoxide reading of ≤10 ppm.Significant change in depressive symptoms on the Beck Depression Inventory-II (BDI-II) from baseline to the end of treatment, and at 3-, 6-, and 12-month follow-up.Significant change in depressive symptoms on the Hamilton Depression Rating Scale (HDRS) from baseline to the end of treatment, and at 3-, 6-, and 12-month follow-up.

### Secondary outcome measures

Continuous abstinence: in accordance with the Russell Standard [56], we will consider that participants have achieved continuous abstinence if they report not having smoked more than five cigarettes from the start of the abstinence period, and have an expired carbon monoxide reading of ≤10 ppm.Reduction of cigarette consumption by 50% or more between baseline and each follow-up will be calculated by the mean number of cigarettes smoked at the end of treatment and in the 7 days prior to the 3-month follow-up. At 6-, and 12-month follow-ups, it will be calculated by the mean number of cigarettes smoked in the past 30 days.Significant change in the Environmental Reward Observation Scale (EROS) scores from baseline to the end of treatment, and at 3-, 6-, and 12-month follow-up.Significant change in the Behavioral Activation for Depression Scale (BADS) scores from baseline to the end of treatment, and at 3-, 6-, and 12-month follow-up.

### Data management and confidentiality

Data will be collected from participants both in paper and electronic format. To make anonymization possible, a unique identity code number for use on trial documents and electronic database will be assigned to each participant. Data collected on paper forms will be kept in a locked filing cabinet. Electronic data will be kept in password-protected computer folders at the Smoking Cessation and Addictive Disorders Unit (University of Santiago de Compostela). Only authorized trial staff will have access to trial documentation.

### Ethical principles

The Bioethics Committee of the University of Santiago de Compostela approved this study, which is registered with the international standard randomized controlled trial number NCT02844595 (www.clinicaltrials.gov). The participants will be provided with both oral and written information regarding the study prior to obtaining their informed consent.

### Statistical analysis

All data analysis will follow the intention-to-treat principle. This conservative approach aims to minimize selection bias through the inclusion in the primary analysis of data from all the participants randomized to each group, including those who drop out of the study.

We will conduct descriptive analysis to summarize the characteristics of the total sample, and the characteristics of the participants in each of the three groups. The main analysis will be a comparison between both active groups and the control group of the proportions of abstinent smokers at the end of treatment, and between BA intervention group and standard intervention group at the end of treatment, and at 3-, 6-, and 12-month follow-ups, through chi-square tests and odds ratios with 95% confidence intervals. A *t*-test analyses will be conducted to determine whether there were any significant differences between the two active treatment groups and the control group in continuous variables such as BDI-II score. We also will conduct mediation analysis, multiple regression analysis, repeated measures ANOVA, and survival analysis.

The study results will be reported in accordance with the Consolidated Standards of Reporting Trials (CONSORT) 2010 statements [58, 59] and Standard Protocol Item: Recommendations for Interventional Trials (SPIRIT) guidelines [60, 61].

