**Method:**

A single blind, three-arm, superiority randomized controlled trial is proposed. Participants will be smokers over 18 years old, who smoke at least 8 cigarettes per day. Participants will be randomized to one of three conditions, using a 2:2:1 allocation ratio: 1) standard cognitive-behavioral smoking cessation treatment; 2) standard cognitive-behavioral smoking cessation treatment plus behavioral activation; or 3) a three-month delayed treatment control group. The primary outcome measures will be biochemically verified point-prevalence abstinence (carbon monoxide in expired air) and significant change from baseline in depressive symptoms to the end of treatment, and at the 3-, 6-, and 12-month follow-up.

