### Sample size and power analysis

Previous studies of cognitive behavioral interventions for smoking cessation [20, 33] and studies of cognitive behavioral interventions for smoking cessation with components targeting depressive symptoms [24, 31] suggest that quit rates after treatment may range between 28% and 61.9%. The sample size for this study was calculated using G*Power3 Software [34]. To detect a 20% difference between the two active groups in the proportion of individuals with tobacco abstinence after treatment, with a power of 80% and a significant *p*-value of 0.05, a total of 102 participants per active group will be required. The sample size of the delayed-treatment control group will be 51 participants. We have chosen an unbalanced design because larger abstinence rates are expected in both active groups as compared to the delayed-treatment control group.

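### Abstinence, BDI-II and HDRS are all primary at four visits, with only a weak priority for abstinence, while the sample size covers one test

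*Protocol article*

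**What the plan says.** - **Aims.** Both abstinence and depressed mood are main aims. Each is a BA-versus-standard comparison at end of treatment and at 3, 6 and 12 months.
- **Primary outcome measures.** Three outcomes are listed: point-prevalence abstinence, BDI-II change and HDRS change ("Significant change in depressive symptoms on the Hamilton Depression Rating Scale (HDRS) from baseline to the end of treatment", with the three follow-ups listed as well). The abstract also gives both domains primary status: "The primary outcome measures will be biochemically verified point-prevalence abstinence (carbon monoxide in expired air) and significant change from baseline in depressive symptoms".
- **Sample size and power analysis.** One comparison is sized: "To detect a 20% difference between the two active groups in the proportion of individuals with tobacco abstinence after treatment". The level is 0.05, the power is 80%, and the result is 102 per active arm.
- **Statistical analysis.** The main analysis compares abstinence at end of treatment in both active groups with control. It also covers abstinence "between BA intervention group and standard intervention group at the end of treatment, and at 3-, 6-, and 12-month follow-ups, through chi-square tests". Effects are given as odds ratios with 95% intervals. A separate sentence plans t-tests of the active groups against control on continuous scores, with BDI-II as the example. Repeated measures ANOVA is then listed among further analyses and is not tied to an outcome.

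The article does not rank the four visits or say whether success needs one primary outcome or all of them.

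**The concern.** Which outcome, visit and contrast carry the confirmatory claim is a protocol-level choice. Here primary status is spread over three outcomes and four visits, while the stated error rate and power belong to one test. As written, a significant abstinence result at any visit, or a mood result at any visit, could be presented as a positive primary finding. The 0.05 would then no longer describe the chance of a false claim that BA adds benefit. Correcting afterwards by splitting alpha equally would take power from the one comparison the trial was sized to detect.

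**Working it through.** **1. The stated sample size is that of one two-sided test.** The inputs from the sample-size section are a 20-point difference, 80% power and 0.05. Neither the base rate nor the sidedness is stated. I assume two-sided testing and 28% v 48%, taking 28% from the low end of the quit-rate range in the same section. With p̄ = 0.38:

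- n = [1.960·√(2·0.38·0.62) + 0.842·√(0.28·0.72 + 0.48·0.52)]² / 0.20² = [1.960·0.6864 + 0.842·0.6717]² / 0.04 = 91.3, so 92.
- With continuity correction, (n/4)·[1 + √(1 + 4/(n·0.20))]² = 101.02, which rounds up to 102.

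This matches "a total of 102 participants per active group will be required". The figure contains no allowance for more than one test. At 40% v 60% the same formulas give 97 uncorrected and 107 corrected.

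**2. Count the tests.**

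- Explicit in the analysis section: 4 BA-versus-standard abstinence tests, plus active-versus-control abstinence at end of treatment (2 tests if done pairwise).
- Implied by the aims and outcome list, but not written as tests: BDI-II and HDRS, BA versus standard, at 4 visits = 8. Together with abstinence that makes 12.
- If all three outcomes were also compared pairwise with control at end of treatment: 6 more, making 18.

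**3. Chance of at least one false positive if each test is at 0.05 and no differences exist.** With independent tests this is 1 − 0.95^k. For correlated tests I use a multivariate normal simulation with arms of 102, 102 and 51. The assumed correlations are 0.3-0.9 between visits, 0.5-0.8 between BDI-II and HDRS, and 0-0.3 between abstinence and mood. None of these is given in the article.

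| Family | Independent | Correlated (assumed) |
|---|---|---|
| 4 abstinence tests, BA v standard | 1 − 0.95⁴ = 18.5% | 9-17% |
| The same plus 2 control tests | 1 − 0.95⁶ = 26.5% | 16-24% |
| 12 tests, BA v standard | 1 − 0.95¹² = 46% | 22-42% |
| 12 plus 6 control tests | 1 − 0.95¹⁸ = 60% | 35-53% |

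**4. Cost of an equal alpha split at 102 per arm.** Power = Φ{[0.20·√102 − z·√(2p̄(1 − p̄))] / √(p₁(1 − p₁) + p₂(1 − p₂))}, without continuity correction. Both pairs of rates are assumptions.

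| Level | z | 40% v 60% | 28% v 48% |
|---|---|---|---|
| 0.05 | 1.960 | 82% | 84% |
| 0.05/3 | 2.394 | 68% | 71% |
| 0.05/12 | 2.865 | 50% | 53% |

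**The case against.** The strongest reply is that a leading test can already be seen. The analysis section calls the abstinence comparison the main one, and the sample size singles out BA versus standard after treatment. That stands in part, so it would be wrong to say that nothing is ranked. It remains a weak priority: the main analysis itself spans four visits and the control comparisons, and the aims and outcome list put mood on the same footing.

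A reader might infer that the plan tests 12 or 18 hypotheses at 0.05 each, with a false positive chance of 25-50% or more. The text does not support this as a statement of fact, for four reasons:

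- The 0.05 level appears only in the sample-size sentence and, by implication, in the 95% intervals for abstinence. For BDI-II and HDRS it is inferred.
- No visit-by-visit BA-versus-standard tests of mood are written down. The t-test sentence concerns the control group and names neither a visit nor HDRS. Repeated measures ANOVA could replace the eight assumed mood tests and lower the error.
- The control comparisons could be pooled or three-group tests. They also inflate the error only if active treatment does nothing, whereas the sample-size section expects higher abstinence in both active arms. BA versus standard is the more relevant family.
- A range of 25-50% is closest to the 12 tests without control, so it cannot also be quoted as including the control comparisons.

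It can also be said that multiplicity methods are often left to an analysis plan, and none is shown here. That covers the choice of adjustment. It does not cover the choice the article does make, to call three outcomes at four visits primary and size for one of them. Whether two main aims must share one error rate is debatable, but even the abstinence aim alone has four unordered visits.

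**Conclusion.** The point holds in a conditional form. Primary standing is given to three outcomes at four visits. Only abstinence after treatment, BA versus standard, has stated error and power, and the article's hints of priority do not settle which result decides the trial. Reading each test at 0.05, the chance of at least one false positive BA-versus-standard claim is about 9-19% on the four tests the analysis section spells out. It reaches about 22-46% only if both depression scales are also tested at every visit. The upper ends assume independence and the lower ends assume strong correlation. Replacing the visit-by-visit mood tests with repeated measures ANOVA would bring the second range down. The structural defect does not depend on these assumptions; its size does.

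**What to change.** State that the primary confirmatory test is CO-verified abstinence, BA versus standard, at end of treatment, at two-sided 0.05. This is the test the sample size already supports. Test any further confirmatory claims at 0.05 in a fixed sequence set before outcome data are analysed, stopping at the first failure. BDI-II at end of treatment followed by 12-month abstinence is one possible order, but the order is the sponsor's choice. Report HDRS, the remaining visits and the control comparisons with confidence intervals and without confirmatory claims.

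The cost is more than a change of wording. It amends the published primary outcomes of a registered trial that is still recruiting, fewer results can be called primary, and a failed step ends confirmatory testing. No participants are added, and the first test keeps the stated 0.05 and its planned power. A Bonferroni split at 102 per arm would instead cut power from about 82-84% to 68-71% over three tests, or to 50-53% over twelve.
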